#### Qualitative study

A purposive sample of eight intervention practices (two in each state that includes a cross section of various practice sizes) will be qualitatively studied. This study will determine what individual and organisational factors explain the success of the PEP intervention and explore the role of the intervention facilitator in supporting practices to make improvements. The qualitative study is broadly informed by a variety of theories and frameworks that help us to understand the organizational routines and patterns of work
[37,38], practice systems
[39-41], and the way in which change is enacted and adapted in practices
[42] and a framework for organization of care activities (Chronic Care Model)
[43]. The study will include qualitative interviews conducted by the field researchers with practice staff involved in the intervention early and late in the intervention process. Other qualitative data will be collected from the intervention facilitators, including a diary of meeting and contacts with the practice, their notes on the implementation of the intervention, and an interview towards the end of the intervention period. Analysis will be conducted with the aid of NVivo using an approach previously trialed by Cohen et al.
[44]. This will characterise narratives of the intervention at each study site looking for variation of key components, focus at each practice, and identifying factors which influence (or are perceived as influencing) the intervention.

#### Study size

The trial is being conducted in 32 practices. We estimate that the number of GPs and PNs recruited to the study will be 80.

We estimate that the records of at least 500 patients will be audited in each practice (i.e., 8,000 total). Assuming a design effect due to clustering of 1.8 based on previous studies
[45], a sample of 188 patients in each group would have sufficient power (β = 0.8 and α = 0.05) to detect a 20% difference in the proportion of patients whose lifestyle and physiological risk factors are recorded. A sample size of 500 would have sufficient power to detect an effect size if 0.3 in recorded BMI (based on ICC = 0.047), LDL-Cholesterol (ICC 0.059), and systolic blood pressure after adjusting for clustering (ICC 0.062)
[29,46,47].

It is estimated that at least 40 patients will be recruited to participate in the patient survey per practice or 640 patients in each arm of the trial. Allowing for 10% loss to follow up at 12 months, this will leave 36 patients per practice (576 in each group). Assuming a design effect due to clustering of two based on previous studies, a sample of 500 patients in each group would have sufficient power (β = 0.8 and α = 0.05) to detect a 15% difference in the proportion of patients offered education for diet or physical activity after adjusting for clustering (ICCs 0.051 and 0.035) and a 10% difference referral (ICCs 0.026 and 0.011). This sample size would have sufficient power to detect an effect size of 0.3 in serves of fruit and vegetables consumed (ICC 0.001) and physical activity scores (ICC 0.018)
[33].

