**Figure 1 F1:**

The 5As conceptual model.

The guidelines have been widely disseminated and well received. However implementation requires more than dissemination
[9], it requires a tailored approach to generate change in clinicians behaviour
[10], and there exists evidence of gaps between the guideline recommendations and their implementation in Australian general practice
[7,11,12]. Some of the reasons for the failure to implement prevention guidelines are related to the complexity of guideline recommendations and patient, practitioner, and practice barriers
[7,13], including lack of capacity to provide brief interventions or refer for more intensive education and support
[14,15]. Patients’ understanding of prevention is variable: they lack knowledge about what preventive care is what is relevant to them, and there is a tendency for patients with low health literacy and education attainment to be less likely to ask for, and therefore to receive, preventive care
[16,17]. The culture of individual practices, their openness to change, and the number and experience of providers, all influence the ability to implement preventive guideline recommendations
[18].

The Preventive Evidence into Practice (PEP) study is a partnership between New South Wales, Flinders, Monash, Bond, and Queensland Universities, the Royal Australian College of General Practitioners (RACGP), the National Heart Foundation of Australia (NHFA), and the BUPA Foundation. The PEP study is a national, cluster randomised control trial of an intervention designed to support general practices to implement the recommendations of evidence-based clinical management guidelines for the prevention of CVD in general practice among patients aged 40 to 69 years.

This study aims to evaluate the impact of the PEP intervention on: The behaviour of doctors and nurses in general practice in assessing and recording risk factors and providing interventions to address these; and patient behavioural and physiological risk factors.

We hypothesise that, for patients aged 40 to 69 years, the PEP intervention measured at the practice level over 12 months will improve: by 20% recording of behavioural and physiological risk factors; by 20% the adherence to the recommendations of guidelines for the management of these risk factors; and by 5% the lifestyle and physiological risk factors of patients with the risk factors.

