	· In the previous 24 months:-	
	o Blood pressure (in patients without hypertension)	
	o Weight (with height for BMI)	
	o Waist circumference	
	o Fasting blood glucose	
	oFasting Lipids	
	· Ever:-	
	o Smoking status	
	o Alcohol intake	
Recalled Advice	Proportion of eligible patients who were at risk who recalled being offered advice:	0 and 12 months
	· Diet (fruit and vegetables, low saturated fat)	
	· Physical activity	
	· Weight control	
Medication	Change in medications over previous 12 months	0 and 12 months
	· lipid lowering,	
	· antihypertensive	
Risk factors	Self assessed:	0 and 12 months
	· Physical activity score*	
	· Diet score**	
	· Smoking Status	
	· Alcohol intake (standard drinks per week)	
	Measured	
	· BMI	
	· waist circumference	
	· blood pressure	
	· lipids (TC, LDL-C, HDL-C, TG).	
Secondary		
GP or nurse preventive care	· Self reported assessment	0 and 12 months
	· Self reported advice	
GP or nurse	· attitudes to preventive care in general practice	0 and 12 months

***** Physical activity level which combines assessment of duration of vigorous and moderate physical activity (scored 0-8, <4 considered at risk)
[36].

****** Serves of fruit and vegetables per day.

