#### Statistical methods

We will examine the change of study variables within the intervention and control practices before and after interventions and compare the difference of outcomes between the two groups after adjusting for baseline differences. Primary analyses will be by intention to treat (patients and practices will be analysed as randomised, rather than by intervention actually received). We will analyse patient variables (risk behaviour, health service use, blood pressure, total cholesterol, HDL, LDL, General Practice Assessment Survey (GPAS) for within and between group differences using multilevel regression techniques adjusted for clustering of patients (level one) within practices (level two). The pre-randomisation value of each outcome will be used as lag covariates. Interactions as well as main effects will be tested. Secondary analysis will compare patients who were referred against those who were not, and defined as at risk. For cases lost to follow up at 12 months, we will conduct sensitivity analyses of the primary and secondary outcomes to determine the effect of their inclusion assuming no change in the outcome variables.

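### Survey power for diet and physical activity advice is computed on all respondents, but the primary outcome counts only patients at risk

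*Protocol article*

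**What the plan says.** The Study size section of the protocol article plans at least 40 survey patients per practice, or 640 per arm. After 10% loss it expects 36 per practice, or 576 per arm. It then states: "Assuming a design effect due to clustering of two based on previous studies, a sample of 500 patients in each group would have sufficient power". The target is to "detect a 15% difference in the proportion of patients offered education for diet or physical activity after adjusting for clustering", with ICCs of 0.051 and 0.035. The printed β of 0.8 is evidently the power.

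Table 1 (Outcome Variables) lists recalled advice under Primary and defines it as: "Proportion of eligible patients who were at risk who recalled being offered advice". Diet, physical activity and weight control are the listed topics.

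The section on participants and recruitment draws survey patients at random from each practice, subject to consent and eligibility; having a behavioural risk factor is not a condition. Study size applies no at-risk fraction and gives no base rate for advice. The only related figure, in the Background, is that 9 in 10 adults have at least one CVD risk factor. That is not a share for diet or for physical activity.

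**The concern.** A power statement describes an outcome only if both use the same denominator. Here the calculation counts every respondent, while the outcome counts only those at risk for the behaviour concerned. The number analysed is 576 (or 500) multiplied by an unstated share. For 500 of the 576 completers to be in the analysis, 500/576 = 87% would have to be at risk.

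If the share is much lower, a null result for recalled advice could be read as coming from a comparison with 80% power when it had less. Table 1 also leaves open whether risk status is taken at baseline or at 12 months. A denominator fixed at 12 months could itself be shifted by the intervention.

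**Working it through.** **Inputs from the article.** 32 practices allocated 1:1, so k = 16 per arm; 500 per arm in the power statement and 576 expected, i.e. 31.25 or 36 per practice; design effect 2; ICC 0.051 (diet) and 0.035 (physical activity); power 0.80; α 0.05.

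**Assumptions.** Two-sided test; 15% read as 15 percentage points; the education offered in Study size taken to be the recalled advice of Table 1; base rates and at-risk shares (neither is given); the same at-risk share in every practice. The rates 42.5% v 57.5% are the least favourable for 15 points.

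**Step 1: the plan's own claim, all respondents.** Effective n = 500/2 = 250 per arm. The number needed without clustering is

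n = [1.96·√(2p̄(1−p̄)) + 0.8416·√(p₁(1−p₁) + p₂(1−p₂))]² / d².

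For 42.5% v 57.5%: (1.3859 + 0.5884)²/0.0225 = 173.2, so 174. Then 174 × 2 = 348, below 500, and power with 250 effective is 92%. With the diet ICC instead of the flat factor of 2, the design effect is 1 + 30.25 × 0.051 = 2.54 for 500 and 1 + 35 × 0.051 = 2.785 for 576. Effective n is 197 or 207, and power is 85% or 86–87%. So with everyone in the denominator the claim of at least 80% holds, with less slack for diet than the factor of 2 suggests.

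**Step 2: at-risk number needed for 80%.** With N at-risk patients per arm spread over 16 practices, effective n = N/[1 + (N/16 − 1)·ICC]. Solving for N:

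N = n(1 − ICC)/(1 − n·ICC/16).

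Diet, 42.5% v 57.5%: 174 × 0.949/(1 − 174 × 0.051/16) = 165.1/0.4454 = 371.

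| Advice | Assumed rates | n | N at risk per arm | Share of 576 | Share of 500 |
|---|---|---|---|---|---|
| Diet | 42.5 v 57.5% | 174 | 371 | 64% | 74% |
| Diet | 20 v 35% | 138 | 234 | 41% | 47% |
| Diet | 10 v 25% | 100 | 140 | 24% | 28% |
| Physical activity | 42.5 v 57.5% | 174 | 272 | 47% | 54% |
| Physical activity | 20 v 35% | 138 | 191 | 33% | 38% |
| Physical activity | 10 v 25% | 100 | 124 | 22% | 25% |

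If the design effect is instead held at 2 whatever the cluster size, the worst case needs 348 at risk: 60% of 576 or 70% of 500.

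**Step 3: power if half are at risk.** From 576, N = 288 at 18 per practice. For diet the design effect is 1 + 17 × 0.051 = 1.867 and effective n is 154. From 500, N = 250 at 15.625 per practice, design effect 1.746, effective n 143.

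| Outcome | Rates or effect | From 576 | From 500 |
|---|---|---|---|
| Diet advice | 42.5 v 57.5% | 75% | 72% |
| Diet advice | 20 v 35% | 84% | 82% |
| Physical activity advice | 42.5 v 57.5% | 82% | 78% |
| Physical activity advice | 20 v 35% | 89% | 87% |
| Fruit and vegetable serves (ICC 0.001) | 0.3 SD | 95% | 92% |
| Physical activity score (ICC 0.018) | 0.3 SD | 88% | 85% |

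At 40% at risk, diet advice at 42.5% v 57.5% has 70% (from 576) or 67% (from 500).

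**The case against.** The strongest reply is that no shortfall has been shown. The article gives neither the at-risk share nor the base rate, and 500 has slack for 15 points. At low base rates about a quarter at risk is enough. If the 9-in-10 figure held for each behaviour, advice power would be at least 83% even in the worst case. Adjustment for the pre-randomisation value of each outcome, planned under Statistical methods, adds power not counted here. All of this stands and makes the size of the problem conditional. It does not repair the denominator: the article prints a power figure for one population and defines the primary outcome in another, so this is more than detail left to an analysis plan.

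A reader might infer more, and the article does not support it:

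- *The survey as a whole is underpowered unless most respondents are at risk.* This holds for diet advice at mid-range base rates, is borderline for physical activity advice, and fails at low base rates.
- *The third hypothesis, "by 5% the lifestyle and physiological risk factors of patients with the risk factors", is underpowered for the same reason.* Its two survey outcomes sized at 0.3 SD keep 80% power down to about 31–43% at risk with the stated ICCs. BMI, LDL-cholesterol and systolic blood pressure are sized on the record audit. The 5% may be relative or absolute, so no power can be attached to it without adding an interpretation.
- *The 10% referral claim fails too.* Referral is not a Table 1 outcome and carries no at-risk denominator. Its power depends on an unstated base rate and on which of two ICCs is used.
- *The primary model will include everyone.* The sentence "Secondary analysis will compare patients who were referred against those who were not, and defined as at risk" concerns a secondary comparison. Table 1 already sets the at-risk denominator for advice, and silence elsewhere does not override it.

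**Conclusion.** The point holds in limited form. Power for a 15-point difference in diet or physical activity advice is computed on all respondents, whereas the primary outcome is confined to patients at risk. The figure as printed does not describe that outcome.

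The consequence is conditional. It is a real loss for diet advice at mid-range base rates if roughly a third or more of completers are not at risk, smaller for physical activity advice, and negligible at low base rates. In the worst case with half at risk, power is 5 to 8 points under the stated 80% for diet, and between 2 points under and 2 points over for physical activity. These sizes rest on the assumed base rates and shares, a two-sided normal approximation, equal at-risk shares across practices, and no gain from baseline adjustment.

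**What to change.** Take the at-risk share and base rate for diet and for physical activity from the baseline survey, which Trial status reports as complete. Restate power, or the minimum detectable difference, for recalled advice on each topic using the expected at-risk number per practice and that topic's own ICC in place of the flat design effect of 2. State the share and base rate used.

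Add one sentence defining the at-risk denominator by baseline, pre-randomisation status, so that the intervention cannot change who is counted.

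The cost is a few restated figures and that sentence. No extra recruitment or data collection is needed. The drawback is that the stated power may become less favourable.

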#### Statistical methods

We will examine the change of study variables within the intervention and control practices before and after interventions and compare the difference of outcomes between the two groups after adjusting for baseline differences. Primary analyses will be by intention to treat (patients and practices will be analysed as randomised, rather than by intervention actually received). We will analyse patient variables (risk behaviour, health service use, blood pressure, total cholesterol, HDL, LDL, General Practice Assessment Survey (GPAS) for within and between group differences using multilevel regression techniques adjusted for clustering of patients (level one) within practices (level two). The pre-randomisation value of each outcome will be used as lag covariates. Interactions as well as main effects will be tested. Secondary analysis will compare patients who were referred against those who were not, and defined as at risk. For cases lost to follow up at 12 months, we will conduct sensitivity analyses of the primary and secondary outcomes to determine the effect of their inclusion assuming no change in the outcome variables.

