**Methods:**

We hypothesise that the intervention will alter the behaviour of clinicians and patients resulting in improvements of recording of lifestyle and physiological risk factors (by 20%) and increased adherence to guideline recommendations for: the management of CVD and diabetes risk factors (by 20%); and lifestyle and physiological risk factors of patients at risk (by 5%). Thirty-two general practices will be randomised in a 1:1 allocation to receive either the intervention or continue with usual care, after stratification by state. The intervention will be delivered through: small group education; audit of patient records to determine preventive care; and practice facilitation visits adapted to the needs of the practices. Outcome data will be extracted from electronic medical records and patient questionnaires, and qualitative evaluation from provider and patient interviews.

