### Randomisation

Practices will be randomly assigned to intervention and late intervention (control) groups after stratification into blocks by state and practice size—i.e., the number of general practictioners (GPs) in a practice—using a computer-generated randomization list. Randomisation will be conducted centrally, after completion of the baseline general practice and practice nurse (PN) surveys, by one of the investigators, a statistician not involved in the data collection or intervention (UJ). Results of the randomisation will communicated to the project management committee prior to the commencement of the intervention.

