#### Participants and recruitment

Eight practices have been recruited by a primary care organisation (Medicare Local) in each of the four states (a total of 32 practices). Staff members from the Medicare Locals approached practices that met the eligibility criteria, such as having computerised medical records to enable an audit of medical records using the Pen Clinical Audit Tool (Pen CAT)
[27] and a PN. Of the 47 practices who expressed interest in the study and who were subsequently visited, 32 agreed to participate, a response rate of 68%. Figure
2 shows the selection and randomisation process.

In each practice, participants include practice staff and patients. As a minimum, at least one GP, one PN and one practice manager from each practice is involved in the study. However, in some of the group practices, two or more GPs are involved in the research. Of the 32 practices involved in the research, only seven are in solo practices whereas 15 of the practices employ five or more GPs and ten of the practices employ between two and four GPs (Figure
4).

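### Randomisation is stratified by state and practice size (the abstract says state only), but the described model names neither factor, so reported intervals may be wider than the design warrants

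*Protocol article*

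**What the plan says.** The two accounts of the randomisation differ. In the abstract, practices are "randomised in a 1:1 allocation to receive either the intervention or continue with usual care, after stratification by state". In the Randomisation section they are allocated "after stratification into blocks by state and practice size", with size defined as the number of GPs in the practice. The size bands used as strata are not given.

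Participants and recruitment says: "Eight practices have been recruited by a primary care organisation (Medicare Local) in each of the four states", 32 practices in total. On size, "only seven are in solo practices whereas 15 of the practices employ five or more GPs", and the other ten have two to four.

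Statistical methods sets out "multilevel regression techniques adjusted for clustering of patients (level one) within practices (level two". It names one set of covariates: "The pre-randomisation value of each outcome will be used as lag covariates". It also says that the analysis will "compare the difference of outcomes between the two groups after adjusting for baseline differences", without listing variables. State and practice size appear nowhere in that section, either as included or as excluded.

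**The concern.** Stratified allocation makes the arms alike on the stratification factors, so differences between strata largely drop out of the treatment contrast. A model with no terms for those factors does not know this. It counts the between-stratum variance as error, and the reported standard error is then larger than the true sampling variation of the estimate.

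This matters more here than in a trial that randomises individuals. There are 16 practices per arm, so practice-to-practice variation drives precision, especially for the record audit with some 500 patients per practice. Four separate primary care organisations, and practices ranging from solo to five or more GPs, are plausible sources of that variation. Both factors are known for every practice. What is at stake is power and interval width, not validity.

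The disagreement between the abstract and the Randomisation section adds to the problem: a reader cannot tell from the article which factors the analysis ought to reflect.

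**Working it through.** **The plan's own figure.** Study size gives 188 patients per group for a 20% difference in recording, with design effect 1.8, 80% power and α 0.05. The base rate is not stated. The continuity-corrected two-proportion formula gives 103 to 107 per group for base rates of 30% to 50%. Multiplied by 1.8, that is 185.4 to 192.6, which brackets 188. The calculation uses no stratification input, so it neither supports nor contradicts the point.

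**Inputs.**
- From the article: 32 practices, eight per state; 7, 10 and 15 practices in the three size groups; at least 500 records per practice; 36 survey patients per practice after 10% loss; ICC 0.062 for systolic blood pressure; ICC 0.051 for one survey outcome, rounded to 0.05.
- Assumed: R, the share of between-practice variance that state and size explain. The documents give no value.

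**Closed form, record audit.** With m patients per practice, the variance of a practice mean, in units of total variance, is

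V(R) = ICC(1 − R) + (1 − ICC)/m.

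At ICC 0.062 and m = 500, V(0) = 0.062 + 0.938/500 = 0.063876. The between-practice part is 0.062/0.063876 = 97%.

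| R | V(R) | V(R)/V(0) | SE ratio |
|---|---|---|---|
| 0.1 | 0.0558 + 0.001876 = 0.057676 | 0.903 | 0.950 |
| 0.3 | 0.0434 + 0.001876 = 0.045276 | 0.709 | 0.842 |
| 0.5 | 0.0310 + 0.001876 = 0.032876 | 0.515 | 0.717 |

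Main effects for four states and three size bands use 3 + 2 = 5 degrees of freedom, so the practice-level count falls from 30 to 25. The 97.5% t quantile rises from 2.042 to 2.060, a factor of 1.008. At R = 0.5 the interval ratio is 0.717 × 1.008 = 0.723, about 28% narrower. At R = 0 it is 1.008, about 1% wider.

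**Simulation, survey outcomes.** This analysed practice means for 32 practices in eight strata of four (four states by two assumed size bands), allocated 2:2 within stratum, with 36 patients per practice, ICC 0.05, no baseline covariate and 20,000 runs.

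| R | Type I error, strata omitted | Type I error, strata included | Interval width, omitted → included | Power at 0.2 SD, omitted → included |
|---|---|---|---|---|
| 0 | 5.1% | 5.0% | 0.395 → 0.399 | 51% → 50% |
| 0.10 | 4.5% | 5.1% | 0.395 → 0.387 | 51% → 53% |
| 0.25 | 3.4% | 4.8% | 0.394 → 0.366 | 51% → 57% |
| 0.50 | 2.0% | 4.7% | 0.391 → 0.328 | 52% → 66% |

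At R = 0.50 the width ratio is 0.328/0.391 = 0.84, about 16% narrower. In the same runs the estimate itself had a standard deviation of 0.0797 under both models. Its average reported standard error was 0.0957 with strata omitted and 0.0793 with them included. The fault is therefore in the reported error, not in the estimate.

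**Main effects instead of full strata.** A second simulation used state plus three size bands of 7, 10 and 15 practices, with an assumed spread of sizes across states and near-balanced allocation. At R = 0.1, 0.3 and 0.5, intervals narrowed by about 4%, 16% and 28% for the audit setting, and by about 2%, 10% and 18% for the survey setting. At R = 0 they were about 1% wider. A share of about 5% was enough to repay the five degrees of freedom.

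**The case against.** The strongest reply is that silence is not exclusion. The article condenses a fuller plan, a complete list of fixed effects usually belongs in that plan, and the sentence about adjusting for baseline differences leaves room for state and size. Data collection procedures also plans to look for patterns of improvement by practice location and size, and Statistical methods says interactions and main effects will be tested. This stands in part. A reader might infer that the trial has decided to leave both factors out; the text does not say so, only that it names neither. But none of these sentences puts the factors in the primary model. A rule aimed at baseline differences is also unlikely to bring in factors that the allocation has already balanced.

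The second reply concerns size. The illustrations use unadjusted ICCs, while the plan includes the baseline outcome, which should already carry persistent differences between states and between large and small practices. The relevant share is what remains after that covariate, and it could be zero. This stands in full.

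Two further inferences are tempting and unsupported. One is that the intervals are invalid in a harmful direction: the simulated type I error with strata omitted never exceeded the nominal level beyond simulation error. The other is that adjustment adds information. At ICC 0.062 the effective number per arm is 8,000/(1 + 499 × 0.062) = 250, and dividing by the variance ratios above gives 277, 353 or 487. The arithmetic is right, but it describes a change in the reported error. Stratified allocation has already delivered the precision.

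A small-sample correction is a separate matter, on which this point shows no defect.

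**Conclusion.** The point holds in a limited form. The abstract and the Randomisation section disagree on the stratification factors, and this does not depend on any unseen plan. The described model names practice clustering and the lagged outcome but neither factor. Followed as written, it gives reported standard errors that are too large whenever state and size still predict outcome after the baseline value. The consequence is conservative: wider intervals and lower power, with no bias and no added false positives.

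The size is unknown. Adjustment would change interval width by anything from about 1% wider (share 0) to about 16% narrower (share 0.5, 36 patients, ICC 0.05, full strata) or up to about 28% narrower (share 0.5, 500 records, ICC 0.062). These results rest on an assumed share, analysis of practice means and no baseline covariate, so the gains are upper-end values and not forecasts for the planned model. The possible loss is small and the possible gain material, which is enough reason to settle the question before the 12-month data are analysed.

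**What to change.** In Statistical methods, add one sentence: the primary models include state and practice size, in the categories used for randomisation, as fixed main effects, alongside the practice random effect and the pre-randomisation outcome. Main effects are preferable to a term for every cell. With three size bands (an assumption), four states would give 12 cells for 32 practices, fewer than three per cell.

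Make the abstract and the Randomisation section agree on the factors, and state the size bands. If the randomisation records show that state alone was used, name only state in both places and in the model.

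The cost is a sentence of analysis wording and a phrase in the abstract. No new data are needed. The statistical price is about five practice-level degrees of freedom (three for state and two for size with three bands), which widens intervals by about 1% if the factors turn out to explain nothing.
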